## **2.0 STUDY OBJECTIVES**

### **2.1 Primary Objectives**

- 2.1.1 To determine the feasibility of fraction reduction for early-stage laryngeal cancer without exceeding the maximum tolerated dose.

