## 4.0 TREATMENT PLAN

### 4.1 Treatment Dosage and Administration

- 4.1.1 This phase I clinical trial will begin with hemilarynx CyberKnife radiotherapy to a dose of 50 Gy delivered in 15 fractions. If this dose/fraction scheme has no dose limiting toxicity, there will be a reduction to 10 fractions to a bio-equivalent dose of 45 Gy. If this dose level is tolerated without dose limiting toxicity, there will be an additional reduction to 5 fractions to a bio-equivalent dose of 42.5 Gy. The patients will also be followed prospectively for voice quality and quality of life. The dose will be prescribed to provide at least 95% planning treatment volume (PTV) coverage.

| Agent         | Pre-medications;
Precautions                                                             | Dose | Route | Schedule                                |
|---------------|---------------------------------------------------------------------------------------------|------|-------|-----------------------------------------|
| Dexamethasone | Pre-medicate with Dexamethasone 1 hour prior to radiation treatments for dose level 1 and 2 | 4 mg | Oral  | Daily 1 hour prior to radiation therapy |

| Dose-Escalation Schedule |                                                                                     |                            |
|--------------------------|-------------------------------------------------------------------------------------|----------------------------|
| Dose Level               | Dose of the Study Agent(s)*                                                         | Minimum Number of Patients |
| Level -1                 | 52.5 Gy in 16 fractions of 3.28 Gy per fraction daily                               | 3                          |
| Level 0                  | 50 Gy in 15 fractions of 3.33 Gy per fraction daily, delivered 5 fractions per week | 3                          |
| Level 1                  | 45 Gy in 10 fractions of 4.5 Gy per fraction daily, delivered 3 fractions per week  | 7                          |
| Level 2                  | 42.5 Gy in 5 fractions of 8.5 Gy per fraction daily, delivered 2 fractions per week | 7                          |

| Toxicity Dose Reductions                                                                                    |                                                               |

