## **10.0 Statistical Considerations**

### **10.1 Primary endpoint**

The primary endpoint of this phase I clinical trial will be to either reach the minimum number of fractions that is tolerated for larynx irradiation or a dose of 42.5 Gy in 5 fractions whichever comes first. Patients will be treated in cohorts of 3-15. Toxicity will be graded using the National Cancer Institute (NCI) Common Toxicity Criteria for Adverse Events (CTCAE) version 4.0. A dose-limiting toxicity (DLT) is a grade 3 or greater toxicity definitely related to treatment in the following categories: laryngeal edema, voice, dyspnea, stridor, or cough. All reported DLTs will be verified by the study

chair, data monitoring committee, and as appropriate, independent review before final determination that a DLT has in fact occurred. The number of fractions will be reduced from 15, to 10 fractions, and then to 5 fractions (reduced by 5 fractions per step). The phase 1 portion of the study will be completed with either of the following events occur: 1) the MTD for a cohort is reached or 2) when the lowest number of fractions is treated and tolerated (42.5 Gy in 5 fractions).

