## 10.2 Phase 1 waiting periods

Fraction reduction for this phase 1 clinical trial will not occur until sufficient waiting has occurred after a cohort has been treated. A period of 90 days must pass before further fraction reduction for the purpose of assessing toxicity. If 90 days have passed without a DLT at a dose level, the trial will be allowed to the next level, so long as either criteria for defining the MTD or criteria for further fraction reduction is not reached. If the maximum number of patients are enrolled to a given fraction level, yet criteria for follow-up is not reached in a representative sample of patients, further enrollment to the protocol will be suspended until adequate follow-up is reached. No action will be taken for Grade 1 or Grade 2 toxicities. If any 2 Grade 3 toxicities occur within a dose level likely or definitely related to radiation therapy, the trial will be terminated with reporting of DLT at that dose level. Any Grade 4 or Grade 5 toxicity found to be likely or definitely related to treatment will result in termination of the trial with reporting of DLT at that dose level.

Grade 3 toxicities likely or definitely related to protocol therapy will result in action in schema provided below:

[figure not shown]

For level -1, if a Grade 3 toxicity occurs, the trial will be terminated with reporting of DLT.

For level 0, if a Grade 3 toxicity occurs, a step de-escalation will occur to level -1. If no grade 3 toxicities are experienced at level 0, the trial will proceed to level 1.

---

For level 1, if there are no Grade 3 toxicities after initial enrollment of 7 patients, an additional 8 patients will be enrolled. If there is no grade 3 toxicity after enrollment of an additional 8 patients, the trial will proceed to level 2. If there is a 1 grade 3 toxicity in the additional 8 patients, the trial will proceed to level 2 at the discretion of the PI and DSMC.

For level 1, if there is 1 Grade 3 in the initial 7 patient cohort, an additional 8 patients will be enrolled. If there is an additional Grade 3 toxicity at this level, the trial will be terminated with reporting of DLT. If there are no further grade 3 toxicities in the additional 8 patients, proceeding to the next level will be done at discretion of the DSMC and PI.

For level 1, if there are 2 grade 3 toxicities in the initial 7 patient cohort, the trial will be terminated with reporting of DLT.

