For level 2, if there are 0 grade 3 toxicities in the initial 7 patient cohort, the trial will enroll an additional 8 patients.

For level 2, if there is 1 grade 3 toxicity in the initial 7 patient cohort, the trial will enroll an additional 8 patients. If there is another grade 3 toxicity, the trial will be terminated with reporting of DLT.

For level 2, if there are 2 grade 3 toxicities in the initial 7 patient cohort, the trial will be terminated with reporting of DLT.

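### The protocol's rules for moving to fewer fractions contradict each other, and the readable text gives no criterion for MTD or tolerated, including for one grade 3 event in 15 at level 2

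*Protocol*

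**What the plan says.** The primary objective (Protocol 2.1.1) is to establish whether fractions can be reduced "without exceeding the maximum tolerated dose". Section 10.1 completes the trial on either of two events: "1) the MTD for a cohort is reached or 2) when the lowest number of fractions is treated and tolerated (42.5 Gy in 5 fractions".

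The general advance rule in 10.2 asks for 90 days without a DLT at the level, and then permits the next level "so long as either criteria for defining the MTD or criteria for further fraction reduction is not reached". Section 4.1.1 says of the 10-fraction level: "If this dose level is tolerated without dose limiting toxicity, there will be an additional reduction to 5 fractions".

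DLT is defined twice. At the end of 4.1 it is grade 4 or 5 laryngeal edema, dyspnea or stridor, probably or definitely related. In 10.1 it is grade 3 or higher, definitely related, in five categories: those three plus voice and cough.

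Section 10.2 then gives rules by level. A common stop rule applies to all: "If any 2 Grade 3 toxicities occur within a dose level likely or definitely related to radiation therapy, the trial will be terminated". Any likely or definitely related grade 4 or 5 event also ends the trial.

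- **Level 1** enrols 7 and then 8 more. With no event in the first 7, "If there is a 1 grade 3 toxicity in the additional 8 patients, the trial will proceed to level 2 at the discretion of the" principal investigator and the monitoring committee. With one event in the first 7 and none in the next 8, advancing is again at their discretion.
- **Level 2** reads: "For level 2, if there are 0 grade 3 toxicities in the initial 7 patient cohort, the trial will enroll an additional 8 patients". With one event in the first 7, 8 more are also enrolled, and a second event ends the trial. Nothing further is written for level 2.

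**The concern.** The trial has one main conclusion: the fewest fractions that patients tolerate. The sentences that lead to it do not agree.

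- The general rule has one limb pointing the wrong way.
- The no-DLT condition conflicts with the level 1 rules under one of the two DLT definitions and not under the other.
- The terms that decide completion, MTD and tolerated, have no written criterion in the readable text.

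If exactly one patient in 15 at the last level has a grade 3 event, two careful readers could reach opposite conclusions from the same data and both cite the protocol. The choice would then be made with the data in view.

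**Working it through.** **1. The plan's own figures.** The study schema gives 17 to 48 patients. From the step table, the minimum is 3 + 7 + 7 = 17 (levels 0, 1, 2) and the maximum is 3 + 15 + 15 + 15 = 48 (levels -1, 0, 1, 2). Both reproduce. No target or expected toxicity rate is stated.

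**2. The general advance sentence.** It has two conditions, each phrased as not reached. Not having reached the MTD criteria is a sensible condition for going on. Not having reached the criteria for further reduction is the reverse of what is needed. Only the second limb is inverted.

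**3. One grade 3 event at level 1, side by side.**

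| Text | Effect of one related grade 3 event |
|---|---|
| 10.2 level 1 rules | Advancing possible at discretion |
| 10.2 general rule and 4.1.1 | Advancing requires no DLT |
| 10.1 definition | A DLT if definitely related and in a listed category |
| 4.1 definition | Not a DLT, since only grades 4 and 5 count |

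Under 10.1 the level 1 rules can permit what the general rule and 4.1.1 forbid. Under 4.1 that conflict disappears, but 4.1 then contradicts 10.1. The attribution wording differs too: definitely (10.1), probably or definitely (4.1), likely or definitely (10.2).

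**4. Terminal outcomes at level 2.** With 7 then 8 patients and a stop at two events, the end states are 0 of 15, 1 of 15, and two or more. The last has a stated action. For 0 of 15 no conclusion is written, but there is no grade 3 event to weigh. For 1 of 15, by either route (0 then 1, or 1 then 0), no conclusion is written. At level 1 both routes have a stated disposition.

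**5. How often 1 of 15 would arise.** Let p be the true probability that a patient has a qualifying grade 3 event. The protocol does not give p, so the values below are assumptions. Patients are taken as independent, with at most one counted event each and no grade 4 or 5 event.

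- P(0 of 15) = (1 − p)^15
- P(1 of 15) = 15 p (1 − p)^14
- P(two or more) = 1 − P(0 of 15) − P(1 of 15)

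At p = 0.05: 0.95^15 = 0.463, and 15 × 0.05 × 0.95^14 = 0.366. Stopping at two events does not change P(1 of 15), because a path with one event never meets the stop rule.

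| Assumed p | 0 of 15 | 1 of 15 | Two or more | 5 fractions tolerated, if 1 of 15 counts | If it does not |
|---|---|---|---|---|---|
| 5% | 0.463 | 0.366 | 0.171 | 0.829 | 0.463 |
| 10% | 0.206 | 0.343 | 0.451 | 0.549 | 0.206 |
| 15% | 0.087 | 0.231 | 0.681 | 0.319 | 0.087 |
| 20% | 0.035 | 0.132 | 0.833 | 0.167 | 0.035 |
| 30% | 0.005 | 0.031 | 0.965 | 0.035 | 0.005 |

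The last two columns differ only in how 1 of 15 is read.

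**The case against.** The best reply is that the protocol works in practice. The level-by-level rules in 10.2 follow the general sentence and show its intent, so the inversion is a drafting slip. The two-event stop rule covers every level, so 15 patients at level 2 with fewer than two grade 3 events and nothing worse would naturally be read as tolerating 5 fractions. Section 10.2 also refers to a decision schema, which is not shown in the text available and may hold the level 2 end state.

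Much of this stands. The intent behind the inverted sentence can be recovered, and the stop rule does suggest that 1 of 15 is tolerated. But that is an inference, and other text points the other way. Section 4.1.1 links toleration to the absence of a DLT, 10.1 can make a single grade 3 event a DLT, and the same count at level 1 is left to discretion. The schema could settle the level 2 result. It would not remove the inverted limb or the disagreement among 4.1, 4.1.1, 10.1 and 10.2, which stand in readable text.

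Three stronger readings are tempting and are not supported:

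- **That the inverted sentence leaves level 2 without a result.** It governs moving to a next level, and level 2 has none. The gap comes from the missing criteria for MTD and tolerated.
- **That the primary endpoint has no result at all at 1 of 15.** The stop rule implies one reading, and the unseen schema may give it.
- **That a stop at level 1 makes a 3-patient level 0 the reported result.** Section 10.2 names no such fallback, and the step table lists 3 to 15 patients at level 0.

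**Conclusion.** The concern holds as a contradiction among decision rules. The second limb of the advance sentence is inverted. The no-DLT condition and the level 1 rules conflict or not according to which DLT definition is used. MTD and tolerated have no criterion in the readable text.

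The ambiguity at 1 of 15 matters most if the true grade 3 rate is low. Its probability is 37%, 34% and 23% at assumed rates of 5%, 10% and 15%, falling to 13% at 20% and 3% at 30%. At a 5% rate the reading chosen moves the chance of a favorable conclusion by 0.829 − 0.463 = 0.366, and at 10% by 0.549 − 0.206 = 0.343. These figures apply to a trial that reaches level 2, rest on assumed rates and on counting patients, and are subject to what the schema shows.

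**What to change.** Three wording changes:

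- **10.2, general rule.** Reword the sentence so that advancing requires the advance criteria to be met and the stop criteria not to be met.
- **4.1, 4.1.1, 10.1 and 10.2.** Reconcile the two DLT definitions, including grade, categories and attribution, with each other and with the advance rules.
- **10.1.** State what MTD and tolerated mean, using the sponsor's own 10.2 rules and counting patients. Give the conclusion to be reported at each terminal outcome, including one affected patient in 15 at level 2 and a stop at level 1. If the schema already gives a level 2 end state, bring it into the text.

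Which count is tolerable, and which DLT definition applies, is for the sponsor to decide; no threshold is proposed here. The cost is an amendment, with no additional patients or assessments.

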### **10.3 Secondary endpoints**

Secondary endpoints for the phase 1 portion of this study include local control, overall survival, functional voice quality, cost-effectiveness, quality of life, and late toxicity (defined as toxicities occurring > 18 months post-treatment).

